## Methods

TOTAL is a cross-sectional, observational study. The protocol for this study was developed using the Strengthening the Reporting of Observational Studies in Epidemiology (STROBE) guidelines [33] and this checklist can be found in S1 Checklist. For Aim 1, RDS will be used to recruit 750 people who use methamphetamine and/or Mandrax. For Aim 2, we will screen and enroll those participants from Aim 1 with TB disease based on positive microbiology (projected 45–75 participants) to estimate the proportion that reflect recent TB transmission via Whole Genome Sequencing (WGS) and social epidemiologic links. For Aim 3, we will enroll 100 participants who are diagnosed with TB and compare PWUD (Arm 1) with people who do not use drugs (Arm 2). For Arm 1 we will recruit 50 participants, most from Aim 2, who have active, untreated pulmonary TB and use methamphetamine and/or Mandrax. For Arm 2 we will recruit 50 persons who do not smoke illicit drugs but have been newly diagnosed with TB disease and have received less than five days of treatment. The study design is shown in Fig 1.

**Fig 1 pone.0262440.g001:**
[figure not shown]
Study design.

The protocol for this study has been approved by the following health research ethics committees: Stellenbosch University (primary institution: N19/10/128), South African Medical Research Council (defers to primary institution of approval) and University of Cape Town (604/2020) and Boston Medical Center Institutional Review Board (H-38910). All participants in this study are informed about the study procedures and agree to participate in this study and informed consent is obtained from all participants. For participants under 18 years old, parental consent will first be obtained prior to informed consent. All methods were performed in accordance with the relevant guidelines and regulations.

### Study site selection

We will recruit participants residing in the greater Worcester area. Worcester is the main town of the Breede Valley municipality in the Western Cape Province, South Africa, and is a prominent wine producing region [34] with high rates of TB and HIV. Though the prevalence of methamphetamine and Mandrax use in this community is not precisely known, both drugs are widely available as reflected in reports from local SUD treatment providers [16]. We recently found that among persons initiating TB treatment and recruited into a prospective research study in the Worcester Community Day Centre (CDC), 53% reported smoked drug use including methamphetamines, Mandrax, and cannabis [35].

### Participant eligibility criteria

Study participants will be recruited by referral chains of PWUD that start with seeds who will be ≥15 years old, reside locally, are willing and able to provide written informed consent and participate in study activities. Inclusion criteria by study arm in shown in Fig 2. For Aim 1, additional inclusion criteria will include self-reported methamphetamine or Mandrax use in the past month and a positive urine drug screen for either of these drugs at enrollment, and a coupon indicating their recruitment into the study by another participant (with the exception of seeds). For Aims 2 and 3, individuals will have microbiologic evidence of active TB disease Xpert Ultra (Cepheid, CA) or *Mtb* culture]. For Aim 3, participants will be excluded if they are pregnant, have taken >5 days of TB medication, or for the control group in Aim 3 Arm 2, if they self-report any past month drug use or have positive urine drug test results. Exclusion criteria for all study aims will include current alcohol or drug intoxication and inability to provide informed consent.

**Fig 2 pone.0262440.g002:**
[figure not shown]
TOTAL participant inclusion criteria per study arm.

### Recruitment and assessment of primary objectives

For Aim 1, we will invite eligible participants to enroll as initial study participants (seeds).

Individuals will provide written informed consent (and parental consent will be obtained for individuals <18 years) before being screened for Aim 1 eligibility. Enrollment will include the collection of biometric fingerprints. Seeds will then complete interviewer-administered biobehavioural questionnaires and provide blood for COVID-19 serology, rapid HIV testing, and host RNA sequencing, and induced sputa for Xpert Ultra and mycobacterial culture respectively. Those with a new HIV diagnosis will be referred to a clinic so that they can access HIV care services. For the latter, sputum will be liquefied and decontaminated (N-Acetyl-L-Cysteine) and neutralized in PBS. The bacilli will be collected by centrifugation, with positive MGIT cultures assessed for acid fast bacilli and Capilia TB Testing to confirm the *Mtb* presence.

Each seed will then be given two coupons to recruit two people with whom they currently use methamphetamine and/or Mandrax. The initial recruits who are successfully enrolled into the study will be given two recruitment coupons to disperse in the same manner. This will continue until we reach 750 participants. Additional seeds will be included as needed until we reach the target sample size (n = 750).

Participants will be asked to return approximately two weeks after their first visit to receive their Xpert Ultra. Detailed contact information will be obtained from participants in order to be able to contact them. If any of the coupon that they disperse result in successful enrollments, they will receive an additional grocery voucher to reimburse them for these efforts. At this time, they will also complete their second RDS interview (to track number of coupons handed out to date). If a participant’s specimen has negative initial TB culture results, we will ask for two additional sputum samples. If the Xpert test is positive and we believe the participant has current TB disease (has not been treated for active TB disease in prior two years which would cause a false positive test results), we will ask them to return to the study site and refer and transport them to their local clinic for confirmation testing and treatment initiation. If the culture results come back as positive at a later stage, participants will be contacted, tracked in the community and asked to come in for a TB result visit. Participants from Aim 1 with evidence of TB disease (i.e., positive Xpert Ultra results and/or positive *Mtb* culture) will be asked to consent to enroll into Aim 2 in which we will estimate the proportion of participants that reflect recent within-network transmission via WGS and social epidemiologic links. Study staff will conduct interviews to identify individual’s social contacts and places of social aggregation. Participants will then provide two additional sputa for additional mycobacterial culture and WGS analysis. One sputum specimen will be stored as raw sputum (for direct DNA extraction), while the other will be decontaminated and used to inoculated MGIT medium as described above. Genomic *Mtb* DNA will be extracted from the MGIT culture, decontaminated sputum remnants or directly from the raw sputum specimen, (following depletion of human and other bacterial DNA) using the hexadecyltrimethylammonium bromide (CTAB) method. WGS analysis will be performed using an Illumina Next-Generation sequencing platform, facilitated by the NIH/NIAID TB Portals Program. If successful, WGS of the DNA extracted directly from sputum will provide analysis of the *Mtb* population structure without culture bias. Altogether, WGS data will be used to identify transmission of *Mtb* among PWUDs.

For Aim 3 Arm 1, 50 PWUD with active, untreated pulmonary TB will be recruited from Aim 2, and if necessary, the rest will be recruited from local health clinics. After providing informed consent, participants will receive a chest radiograph and undergo bioaerosol sampling. In Aim 3 Arm 2, study staff will recruit patients recently diagnosed with active TB disease who initiated treatment less than five days prior, or who are scheduled for treatment initiation from medical records at local health clinics, if they have provided permission to be contacted for this study. Study materials will also be placed within clinics and hospitals in the Worcester area so that individuals can contact study staff directly. Once individuals are screened for eligibility, informed consent is obtained and participants are enrolled, participants will then complete all study procedures that Arm 1 participants completed in Aim 2 and also undergo the Aim 3 procedures previously described.

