## Abstract

People who use illicit drugs (PWUDs) have been identified as a key at-risk group for tuberculosis (TB). Examination of illicit drug use networks has potential to assess the risk of TB exposure and disease progression. Research also is needed to assess mechanisms for accelerated TB transmission in this population. This study aims to 1) assess the rate of TB exposure, risk of disease progression, and disease burden among PWUD; 2) estimate the proportion of active TB cases resulting from recent transmission within this network; and 3) evaluate whether PWUD with TB disease have physiologic characteristics associated with more efficient TB transmission. Our cross-sectional, observational study aims to assess TB transmission through illicit drug use networks, focusing on methamphetamine and Mandrax (methaqualone) use, in a high TB burden setting and identify mechanisms underlying accelerated transmission. We will recruit and enroll 750 PWUD (living with and without HIV) through respondent driven sampling in Worcester, South Africa. Drug use will be measured through self-report and biological measures, with sputum specimens collected to identify TB disease by Xpert Ultra (Cepheid) and mycobacterial culture. We will co-enroll those with microbiologic evidence of TB disease in Aim 2 for molecular and social network study. Whole genome sequencing of *Mycobacteria tuberculosis* (*Mtb*) specimens and social contact surveys will be done for those diagnosed with TB. For Aim 3, aerosolized *Mtb* will be compared in individuals with newly diagnosed TB who do and do not smoke illicit drug. Knowledge from this study will provide the basis for a strategy to interrupt TB transmission in PWUD and provide insight into how this fuels overall community transmission. Results have potential for informing interventions to reduce TB spread applicable to high TB and HIV burden settings.

**Trial registration:** Clinicaltrials.gov Registration Number: NCT041515602. Date of Registration: 5 November 2019.

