### Assessment of primary objectives

For the primary analysis, TB prevalence among PWUD will be estimated according to the Volz-Heckathorn estimator [56]. Analysis will be performed using the RDS package within R (r-project.org) and sensitivity analysis will be implemented using the SS estimator. Prevalence of TB among PLHIV and those without HIV will be estimated and compared to community survey estimates [57].

For the second aim, we will estimate the prevalence of clustered cases via WGS in our population of PWUD and check additional thresholds to confirm robustness. A combination of software packages has previously been assembled with optimised parameters, together with in-house developed scripts, to create a customised pipeline for the analysis of mycobacterial genomes, with specific focus on variant calling. This customised pipeline has been automated for *Mtb* WGS data analysis [58]. An in-house developed script is used to identify the variants, and high confidence single nucleotide polymorphisms are then used in further analyses. Phylogenetic software will be used including RaxML, IQ-TREE and MEGA, and phylogenomic trees will be visualised using FigTree software [59–61]. For clustering analysis, the single nucleotide variants used for phylogenomic inference will be used to determine the variant distances between isolates and cluster analysis will be performed with the R-programming language, implementing the APE (Analyses of Phylogenetics and Evolution) and ADEGENET (Exploratory Analysis of Genetic and Genomic Data) packages.

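### The protocol calls a positive Xpert in recently treated people a false positive, yet its only stated definition of TB disease counts them as cases

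*Protocol article*

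**What the plan says.** All references are to the protocol article.

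- **Recruitment and assessment of primary objectives, return and referral step.** A positive Xpert leads to return and referral if staff believe the disease is current, which is explained as meaning that the participant "has not been treated for active TB disease in prior two years which would cause a false positive test results".
- **Same section, a few sentences later.** Aim 1 participants are invited into Aim 2 if there is "evidence of TB disease (i.e., positive Xpert Ultra results and/or positive *Mtb* culture". Recent treatment is not mentioned.
- **Participant eligibility criteria.** For Aims 2 and 3, "individuals will have microbiologic evidence of active TB disease Xpert Ultra (Cepheid, CA) or *Mtb* culture", again with no exception. On who is kept out of every aim: "Exclusion criteria for all study aims will include current alcohol or drug intoxication and inability to provide informed consent". Earlier TB treatment is therefore no bar to Aim 1.
- **Abstract.** TB disease in the enrolled sample is identified through "sputum specimens collected to identify TB disease by Xpert Ultra (Cepheid) and mycobacterial culture".
- **Assessment of primary objectives.** The primary analysis names the Volz-Heckathorn estimator of TB prevalence but not the numerator. It adds: "Prevalence of TB among PLHIV and those without HIV will be estimated and compared to community survey estimates". The Primary objectives section hypothesises that prevalence is significantly higher in people who use drugs (PWUD) than in the survey.

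**The concern.** Take a participant who finished TB treatment last year and is Xpert-positive and culture-negative. Under the referral wording this is a false positive. Under the disease definition it is a TB case. Both statements stand in one section, and nothing says which governs the data.

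Two results are exposed. In Aim 2 the effect is explicit: the and/or rule is the entry rule, so such a person joins the active TB cases among whom the share due to within-network transmission is estimated. A negative culture does not remove them, because DNA may also be extracted from raw sputum or decontaminated remnants. In Aim 1 the effect is inferred: if the same rule supplies the numerator, each such person adds a case on the PWUD side, in the hypothesised direction. If the choice is left until results are known, it could settle the primary comparison.

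**Working it through.** **1. The plan's own figure.** Sample size assumptions gives n = 750, a 2.6% baseline and 80% power for 7.2% at design effect (DE) 4, or 5.7% at DE 2. The 2.6% is worded as prevalence of drug use but serves as the baseline of the TB comparison, and I use it so. Alpha and sidedness are not stated. I assume a one-sample exact binomial test with upper tail 0.025.

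- DE 4: effective n = 750/4 = 187.5, taken as 187. Reject at 11 or more cases. Power at 7.2% = 79.6%, which reproduces the stated 80%.
- DE 2: effective n = 750/2 = 375. Reject at 17 or more cases. Power at 5.7% = 86.3%, so the stated 80% is conservative here.

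A normal approximation (score test) gives 89.1% at DE 4 and does not reproduce the plan, so the exact test is used below.

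**2. Planned detectable excess.** 5.7 − 2.6 = 3.1 points (DE 2) and 7.2 − 2.6 = 4.6 points (DE 4).

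**3. False cases added.** Let r be the share of participants treated in the prior two years and f the share of those who are Xpert-positive and culture-negative without current disease. Neither is in the documents. Assumed ranges: r = 5-15%, f = 5-20%.

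Added prevalence = r × f; added cases = 750 × r × f.

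- Low: 0.05 × 0.05 = 0.25 point; 750 × 0.0025 = 1.9, about 2 cases.
- High: 0.15 × 0.20 = 3.0 points; 750 × 0.03 = 22.5, about 23 cases.

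Counting only people without current TB multiplies these by 1 − 0.026 = 0.974 (1.8 and 21.9 cases), which changes nothing of substance. The plan expects 30-90 TB cases in Aim 1.

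**4. Chance of declaring an excess when the true prevalence is 2.6%.** This is P(X ≥ 17) for n = 375 and P(X ≥ 11) for n = 187 or 188, at the apparent prevalence.

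| Added points | Apparent prevalence | DE 2 | DE 4 |
|---|---|---|---|
| 0 | 2.6% | 2% | 1% |
| 0.25 | 2.85% | 4% | 2% |
| 0.5 | 3.1% | 8% | 3% |
| 1.0 | 3.6% | 20% | 8% |
| 2.0 | 4.6% | 56% | 24-25% |

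The normal approximation would give 26% / 17% at +1 point and 64% / 43% at +2 points. With only about 5 expected cases at DE 4 (187.5 × 0.026 = 4.9) it overstates the risk.

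**5. Direction.** Adding these people to the numerator cannot lower PWUD prevalence. If the survey counted Xpert positives in the same way, part of the bias cancels in the comparison. It would not cancel fully if recent treatment is commoner among PWUD.

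**The case against.** The strongest reply is that the and/or wording is written as the gate to Aim 2, and no sentence makes it the Aim 1 numerator. A condensed article may leave that numerator to a full protocol or SAP. The authors plainly know the artefact, and cultures and medical history would let them handle it. This stands in part: inflation of the Aim 1 estimate is an inference, though a strong one, since no other definition of TB disease is given. It does not rescue the Aim 2 gate, which is explicit and conflicts with the referral wording.

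A second reply is that the size rests on assumed rates and may be negligible. That stands: at the low end the chance of a false excess is 4% / 2%, little above the test's own error.

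A reader might infer more than the documents support:

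- **Repeat sputa.** The request after "negative initial TB culture results, we will ask for two additional sputum samples" might look like a further source of inflation. Extra sputa find more true cases. They would bias the comparison only if the survey sampled less, which is not stated. Restricting the count to enrolment-visit sputum could bias the other way.
- **Age and sex mix.** Lack of standardisation to the survey is a matter commonly left to a SAP, and the survey's composition is not given. Results by HIV status are already planned.
- **Residual DNA.** It might be said that it cannot reflect recent transmission. Disease treated within two years may itself have been acquired recently in the network. All that follows is that, on the protocol's own reasoning, the person is not a current active case.

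**Conclusion.** The contradiction is real and lies in the stated text. As written, the rule admits to Aim 2, as active TB, people whose positive Xpert the protocol itself regards as false, and it probably admits them to the Aim 1 prevalence as well. The documents do not establish that the prevalence will in fact be inflated, or by how much. Under the assumed rates the effect runs from minor (+0.25 point, about 2 cases) to nearly the excess the study is designed to detect at DE 2 (+3.0 against 3.1 points). The error rates rest on a true prevalence of 2.6%, a fixed community value, an exact test with upper tail 0.025, and effective sample sizes of 375 and 187-188. The repair is cheap, and it must come before results are seen, so it is worth making even though the size is unknown.

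**What to change.** 1. Reconcile the referral wording with the disease definition in Recruitment and assessment of primary objectives, and carry the result into Participant eligibility criteria.
2. Fix one research case definition for the Aim 1 prevalence and the Aim 2 analysis set before results are seen: a person treated for TB in the prior two years counts as a case only if culture-positive; for everyone else, Xpert Ultra and/or culture as now.
3. Report prevalence counting all Xpert positives, and prevalence counting only culture-confirmed cases, as sensitivity analyses.
4. Compare with the community survey under the same definition where its data allow, and say so where they do not.

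This concerns the research case definition only. Whom to refer is for the investigators, and no clinical rule is proposed.

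The cost is wording. Culture is already done, and Table 1 lists medical history for Aim 1; the referral rule already needs to know about treatment in the prior two years. The downside is slightly fewer cases in Aims 1 and 2, and a few true relapses with negative culture may be missed. The all-Xpert-positive analysis shows how much that matters.

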### Exhaled bioaerosol collection

For Aim 3, exhaled bioaerosols will be collected with a modified Coriolis®μ Air Sampler, developed to quantitate the infectiousness of expired air [36]. This Respiratory Air Sampling Chamber (RASC) is used to collect and concentrate biological airborne particles (0.5–20 μm) using a high-flow wet walled cyclone, as previously described [37], with some modifications which include reducing the sampling period to two consecutive 15-minute sessions and the removal of continuous CO_2_, aerodynamic particle, temperature, and humidity monitoring. Droplet digital polymerase chain reaction (ddPCR) analysis will be used to detect *Mtb* within the exhaled air [38].

### RNA sequencing

RNA will be extracted from PAXgene tubes collected during Aim 2 or Aim 3 Arm 2 study procedures, and complimentary or cDNA prepared using an automated mRNA extraction, which would be done with a Hamilton EasyBlood Star at Stellenbosch University and cDNA synthesis procedure together with the PAXgene Blood RNA Kit (Qiagen, Germany). We will use the Fluidigm microfluidic qRT-PCR platform to evaluate the expression of genes selected from different published TB transcriptomic biosignatures, using TaqMan primer-probes. Assays will be run on either the 96.96 or 192.24 Gene Expression chips (Fluidigm) on a Biomark HD multiplex microfluidic qRT-PCR instrument. Analysis of gene expression data, including PCR controls and assessment of internal quality control samples to monitor performance of assays across individual Gene Expression chips, and computation of signature scores will be done with pre-prepared R scripts [39–41]. We will look for prevalence of the 16-gene host RNA signature previously studied by other research institutes in Worcester [32, 42], as well as other available signatures shown to be associated with higher risk of disease progression.

### Substance use and biobehavioural measures

TOTAL uses validated self-report questionnaires to assess patterns of substance use (Table 1). The Alcohol, Smoking and Other Substance Involvement Screening Tool (ASSIST) [43], Timeline Follow Back (TLFB) technique for drug use [44], and a modified version of The Important People Instrument [45], which assesses substance use within the participant’s social network, will capture substance use behaviour including frequency, quantity, patterns, and types of substances used. Participants who are identified as high risk for problems due to their substance use according to the ASSIST will be offered a referral to local treatment services.

**Table 1 pone.0262440.t001:** Biobehavioral assessments at study visit time periods.

	Assessment Measures										
	Biological Measures and Specimen Collection				Behavioural assessment	Psychosocial Measures			Biological assessment		RDS
Aim 1	Rapid Testing		Sputum for Xpert Ultra, Mtb Culture		Substance Use Measures	Mental health measures	MOSS-S (Medical Outcomes Social Support Survey)	Household Hunger Survey	TB symptom screen	Medical History (including HIV risk behaviour)	*Network Size
	*urinalysis for meth/Mandrax										*RDS rejection recruitment questionnaire
					*ASSIST (Alcohol, Smoking, Substance Use Involvement Screening Tool)	*CESD					*important people survey
	*blood for rapid HIV test		Blood for Host RNA Signature Measurement and COVID-19 Serology			*K-10					
					* Timeline Follow back (Meth/Mandrax)						
Aim 2			Sputum collection for Mtb culture and WGS (whole genome sequencing)								*social contact survey
											*important people survey
Aim 3a	Rapid Testing	Chest radiograph		Bioaerosol assessment *Respiratory Air Sampling Chamber (RASC)							
	*urinalysis for meth/Mandrax										
	*pregnancy test										
Aim 3b	Rapid Testing	Chest radiograph	Sputum collection for Mtb culture and WGS (whole genome sequencing), Blood for Host RNA Signature Measurement and COVID-19 Serology	Bioaerosol assessment *Respiratory Air Sampling Chamber (RASC)	Substance Use Measures	Mental health measures	MOSS-S (Medical Outcomes Social Support Survey)	Household Hunger Survey	TB symptom screen	Medical History (including HIV risk behaviour)	*Social contact survey
	*urinalysis for meth/Mandrax										
					*ASSIST (Alcohol, Smoking, Substance Use Involvement Screening Tool)^a^	*CESD					
	*pregnancy test					*K-10)					

Depressive symptoms will be screened for using The Center for Epidemiologic Studies Depression Scale (CES-D) [46], while the K-10 Kessler Psychological Distress Scale will be used to assess general psychological distress [47]. The Medical Outcomes Survey’s Social Support Scale [48], HIV risk-taking behaviour scale [49] and the Household Hunger Scale will also be used. Validity of these scales has been demonstrated in South Africa which have been widely used in populations of PLHIV/TB who use alcohol or other drugs [50–52]. Referrals will also be made if there are any concerns about individual’s mental well-being.

We will use the World Health Organization (WHO) four-symptom screening (current cough, a cough lasting ≥2 weeks, weight loss, night sweats, or fever) to evaluate for clinical versus subclinical TB [53].

